### Frequency and plans for auditing trial conduct {23}

There are two main areas where periodic audit procedures will take place: the clinical interaction among clients and therapists, and data integrity. All the therapy sessions will be audio-recorded, and then 10% of those will be randomly analyzed to check intervention fidelity. Also, by the end of each session, the client will report on the therapeutic alliance using a validated tool. Both procedures are meant to control the quality of the interventions being provided. Regarding data integrity, a research assistant with training in data supervision will verify the consistency and completeness of data each month.

### Plans for communicating important protocol amendments to relevant parties (e.g., trial participants, ethical committees) {25}

Any significant change to the protocol will require a formal amendment presentation to the ethics committee of the Pontificia Universidad Católica de Chile. Such amendments include, among others, changes to the primary outcome, sample size calculations, eligibility criteria, methods for blinding and allocation concealment, and statistical analysis.

### Dissemination plans {31a}

This trial originated from the collaborative work between our research team and the National Agency for Alcohol and Drugs (SENDA, its Spanish acronym). Additionally, the local primary care health services are providing critical support to the study. This proximity between our research team and the stakeholders should make dissemination easy, especially for the local context. In this regard, we will hold regular meetings with local stakeholders throughout the study and at least one meeting with SENDA to share the results at the end of the study.

Furthermore, as the results may be of interest to other PC services that address alcohol use disorders, we will publish the results in an international journal. The goal is to have the main manuscript submitted within 1 year from trial closure.

## Discussion

The present study will provide initial evidence on the effect of a brief psychosocial treatment for AUD in PC, which is essential in the context of the improved response capacity to harmful alcohol use through the SBIRT programs. The evidence on the effectiveness of such therapies in PC is still scarce, and this trial attempts to provide valuable information on the topic.

Based on previous reports [3, 4, 13], we hypothesized that the BMT would induce at least a 26% reduction of alcohol consumption compared to EUC. We think this is a reasonable superiority margin, over which the BMT could be further considered for incorporation into PC in Chile. The hypothesis will be tested by the analysis of the primary outcome, i.e., the change in the pattern of alcohol use 6 months after recruitment. We are aware that a binary response outcome would have been of more clinical significance; however, this test would have required a larger sample size, so it did not seem appropriate for an exploratory trial.

Some important modifying and predictive variables have been included to explain the results. The severity of the AUD is of cardinal importance since we do not expect BMT to be equally effective in all the spectrum of the disorder. Even though severity did not mediate MET effectiveness in the MATCH project [38], we have to bear in mind that the MATCH study occurred in specialized care settings and not in PC. In addition, PC is supposed to provide care for prevalent disorders in their mild to moderate presentations, so the question about the severity is of high relevance. Other essential modifiers are the fidelity to the intervention and the therapeutic alliance since both have shown to predict the effect of psychosocial interventions [39].

We devised BMT as a psychosocial intervention based on the best evidence available for effectiveness. Its procedures and strategies are an adaptation of the MET, a manualized therapy of well-proven effectiveness. Even though these procedures have been described in detail [19], it remains a reasonable question whether a general psychologist in PC will be able to provide the therapy with sufficient proficiency. Also, we assume that the participants receiving the BMT will be able to access additional services necessary for their recovery, for instance social services, physician consultations, among others. The study will provide some insights into how these factors mediate treatment effects on PC. Furthermore, the trial will describe to what extent the BMT adds therapeutic benefit to current care in PC.

In conclusion, this trial was conceived with a pragmatic approach, aiming to inform policymakers about the benefit of including a brief psychosocial treatment into PC.

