**Methods:**

A parallel-group, single-blinded, severity-stratified, randomized clinical trial will test the superiority of BMT over enhanced usual care. Eligible participants will be those seeking treatment and who fulfill DSM-V criteria for alcohol use disorder and criteria for harmful alcohol use. With an estimated a loss to follow-up of 20%, a total of 182 participants will be recruited and equally randomized to each treatment group. The intervention group will receive an adaptation of the motivational enhancement therapy, as manualized in Project MATCH. This treatment consists of four 45-min sessions provided by a general psychologist with at least 3 years of primary care experience. The primary outcome is the change from baseline in the drinks per drinking day during the last 90 days, which will be captured using the Timeline Follow Back method. Secondary outcomes will describe the changes in alcohol use pattern, motivational status, and severity of the disorder.

All participants will be analyzed according to the group they were allocated, regardless of the treatment actually received. Mean differences (MD) will be computed for continuous outcomes and relative risks (RR) and RR reductions (RRR) for dichotomous results. Linear models will deliver the subgroup analyses. Missingness is assumed to be associated with the baseline alcohol use pattern and severity, so a multiple imputation method will be used to handle missing data.

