### Outcomes {12}

#### Primary outcome

The primary outcome is the change from baseline in the drinks per drinking day (DDD) during the last 90 days (i.e., the previous 12 weeks), measured at 6 months follow-up. The DDD will be aggregated using means.

The DDD constitutes a relevant outcome because the frequency and quantity in which alcohol is consumed mediate the occurrence of behavioral disorders and health deterioration in clients with AUD. Even though a more comprehensive result, such as clinical recovery or improved quality of life, would be of more clinical significance, these outcomes exceed a short-term, exploratory trial. We have chosen DDD because it has shown to be sensitive to treatment and because it allows comparability with influential clinical trials [21].

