### Participant timeline {13}

### Sample size {14}

Given that there is a spontaneous reduction of alcohol consumption in control groups of 14% [26], and that the reduction attributed to psychosocial treatments in the literature is around 40% [27], we set a superiority margin δ of 26% reduction in alcohol consumption. The following two hypotheses correspond to the superiority test:
H_0_: DDD_EUC_ − DDD_BMT_ = < δ;H_a_: DDD_EUC_ − DDD_BMT_ > δ.

We used local data and the results of project MATCH as references for sample size calculation. Project MATCH [13] recruited participants with AUD in the outpatient setting and observed a standard deviation (SD) of 6.29 drinks, which is similar to reports in Chilean PC [28]. On admission, participants in the MATCH study consumed 11.5 DDD, which should be similar in our population. We expect a decrease of 14% in the EUC group [26], that is, to 9.89 DDD, and a reduction to 40% in the intervention group [27, 29], that is, a decrease to 6.9 DDD.

The sample size was obtained using the formula for means comparison in superiority studies of parallel groups, according to the methodology described by Chow [30]. The computation was made using the R statistical software [31] with the package provided by the same author [30, 32]. We obtained a sample size of *n*_1_ = *n*_2_ = 76 using the following parameters: *α* = 0.05; *β* = 0.2 : *σ* = 6.29; *δ* = 2.99; *κ* = 1 (where *α* is the type 1 error, [1- *β*] the power, *σ* the standard deviation, *δ* the expected difference between both groups, and *κ* the allocation ratio between both groups).

Considering an expected loss to follow-up of 20%, we will have to recruit 91 participants for each group, which is 182 participants in total.

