## Data collection and management

### Plans for assessment and collection of outcomes {18a}

#### Primary outcome

The DDD during the last 90 days will be obtained using the Timeline Follow Back [33] (TLFB) procedure. The TLFB uses a calendar with key dates as memory aids to enhance recall. This method will also record other treatments that the participants received and capture the alcohol use pattern, which is defined as the typical number of drinks consumed in a drinking occasion in the previous 90 days, the frequency of heavy drinking days during the last 90 days (> 4 standard drinks in women and > 5 in men), and the total number of standard drinks consumed in a week during the last 90 days. The reliability of these measurements using TLFB lies between 0.7 and 0.9 [33].

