**1) Primary**			
a) Drinks per drinking day at 6 months	BMT reduced outcome from baseline to 6 months	Drinks per drinking day during the last 90 days in the Timeline Follow Back [continuous]	*T* test

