**2) Secondary**			
a) Alcohol use pattern at 6 months	Back to a low-risk use or abstinence after the treatment	Presence of a low-risk pattern: less than 100 g of ethanol a week and no binge drinking occasions (i.e., more than three SD in women and 4 in men) during the last 90 days in the Timeline Follow Back [binary]	Chi-squared test
b) Frequency of heavy drinking at 6 months	Reduction	Number of heavy drinking occasions (i.e., more than three SD in women and more than four in men) during the last 90 days in the Timeline Follow Back [continuous]	*T* test
c) Most extended period of abstinence during the last 3 months	Augmentation	Number of days of abstinence within the last 90 days in the Timeline Follow Back [continuous]	*T* test
d) Severity of dependency at 6 months	Reduction	Score in the Alcohol DAYS, SEV, and WORST SEV score in the Substance Dependence Severity Scale (last 30 days) [continuous]	*T* test
e) Alcohol related negative consequences	Reduction	Total consequences score in the Drinker Inventory of Consequences [continuous]	*T* test

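### The primary comparison is defined as change in drinks per drinking day but tabulated and sized as the 6-month level, and as unadjusted t tests the two can disagree

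*Protocol article*

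**What the plan says.** The primary comparison is described in these places:

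- **Abstract, Methods:** "The primary outcome is the change from baseline in the drinks per drinking day during the last 90 days".
- **Outcomes {12}, Primary outcome:** "The primary outcome is the change from baseline in the drinks per drinking day (DDD) during the last 90 days", assessed at 6 months.
- **Table 1, row 1a:** the row is titled "a) Drinks per drinking day at 6 months" and the measure is "Drinks per drinking day during the last 90 days in the Timeline Follow Back [continuous"; neither subtracts baseline. The hypothesis cell does refer to a reduction between baseline and month 6. The method is a t test.
- **Sample size {14}:** the alternative hypothesis is "DDD_EUC_ − DDD_BMT_ > δ". The figures are follow-up levels, 9.89 for EUC and 6.9 for BMT, both derived from a baseline of 11.5. The SD of 6.29 comes from Project MATCH and is not described as an SD of change.
- **Discussion:** "The hypothesis will be tested by the analysis of the primary outcome, i.e., the change in the pattern of alcohol use 6 months after recruitment".

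Adjustment for baseline variables appears in Table 1 only as a sensitivity analysis (row 4b).

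**The concern.** A t test on the change score and a t test on the 6-month value are different tests of the same data. They have different standard errors, and they respond differently to a chance baseline imbalance between the arms. Both have support in the text: change in the Abstract and Outcomes section, level in the title and measure of the table row that gives the method, and in the sample size section. A statistician who follows the protocol could run either one and report it as primary.

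At stake are the p value on which the trial's conclusion rests and the power the trial has. If the SD of 6.29 belongs to the level, the sample size calculation does not establish the power of the change score. This is a contradiction between current statements in the article, not a detail left for a later analysis plan. Such a plan would have to choose between them.

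**Working it through.** **Inputs from Sample size {14}:** baseline 11.5; reductions of 14% and 40%; SD 6.29; difference 2.99; α = 0.05; β = 0.2; 76 per group before loss to follow-up.

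**Assumptions, not in the protocol:** the same SD at baseline and 6 months; normal data; a two-sided 5% test against no difference, as an ordinary t test does; a baseline to 6-month correlation r from 0.3 to 0.7. The printed hypotheses use δ as a margin; that is a separate matter and is not examined here.

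**1. The plan's own figures.** 11.5 × 0.86 = 9.89; 11.5 × 0.60 = 6.90; difference 2.99. These reproduce. The size of 76 does not: 2 × [6.29 × (1.960 + 0.842) / 2.99]² = 69.5, so 70 per group two-sided, or 55 one-sided. That too is a separate matter; 76 is used below because it is the plan's stated number.

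**2. Same target.** With a shared baseline, the changes are 11.5 − 9.89 = 1.61 and 11.5 − 6.90 = 4.60. Their difference is 4.60 − 1.61 = 2.99, equal to the difference in levels.

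**3. Different precision.**
- Level: SE = 6.29 × √(2/76) = 1.02. Power = Φ(2.99/1.02 − 1.96) = 83.4%, whatever r is.
- Change: SD = 6.29 × √(2(1 − r)), used in the same formula.
- Baseline-adjusted level: SD = 6.29 × √(1 − r²).

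| r | SD of change | Power, level | Power, change | n per arm for 80%, change | Power, baseline-adjusted |
|---|---|---|---|---|---|
| 0.3 | 7.44 | 83.4% | 69.7% | 98 | 86.7% |
| 0.5 | 6.29 | 83.4% | 83.4% | 70 | 92.3% |
| 0.7 | 4.87 | 83.4% | 96.6% | 42 | 98.4% |

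**4. Where the change score drops below 80%.** At 76 per arm, 80% power needs an SD of at most 6.579. Setting 2(1 − r) = (6.579/6.29)² = 1.094 gives r = 0.45. Below that the raw change score misses its planned power; at r = 0.2 it has 63.9% and would need 112 per arm.

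**5. How often the two tests disagree at 5%.** Simulated trials with a true difference of 2.99 and 76 per arm, the two tests applied to the same data:
- Two-sided t tests, 10,000 trials per setting: 24.8% (r = 0.3), 20.0% (0.5), 17.7% (0.7).
- Known-variance version, 40,000 trials: 24.7%, 20.2%, 16.8%.

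Even at r = 0.5, where the two powers are equal, about one trial in five gives opposite verdicts.

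**The case against.** The strongest reply is that the definition is clear. The Abstract and the Outcomes section both say change. The hypothesis cell of row 1a also looks back to baseline. Table 1 likewise omits the word change for the SDSS and DrInC scores, which the Outcomes section defines as changes, so its measure column may simply name the instrument score. This stands in part: row 1a is mixed, not a pure level specification. But its title and measure do not say change, and the hypotheses and SD are not tied to a change score.

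Three stronger readings are tempting and are not supported.

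- **That the Discussion makes a secondary outcome the deciding one.** The term it uses is defined elsewhere: under {18a} the calendar method is also to "capture the alcohol use pattern, which is defined as the typical number of drinks consumed in a drinking occasion in the previous 90 days", with two further measures, and Table 1 lists "a) Alcohol use pattern at 6 months" as a binary secondary outcome. But the Discussion sentence refers back to the primary outcome already defined, and the next sentence says a binary outcome was not chosen. It is loose wording.
- **That level and change estimate different effects.** Step 2 shows that they do not. The conflict concerns variance and chance baseline imbalance.
- **That the trial's false-positive rate is about 9%.** With no effect, the chance that at least one test is significant is 8.8% to 9.4% over the same correlations. That applies only if both are run and the favourable one is reported. The protocol does not plan this; it has a statistician blinded to allocation and requires a formal amendment for changes to the primary outcome or analysis. These safeguards reduce the risk but do not say which test is primary.

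**Conclusion.** The inconsistency is real and should be corrected, in this limited form: the protocol supports both change in DDD and DDD at 6 months as the primary comparison, under an unadjusted t test for which the choice matters. At 76 per arm the level test has 83% power, against 70% to 97% for the change test over correlations of 0.3 to 0.7. The two would disagree on significance in roughly 17% to 25% of trials at the design effect. These sizes rest on the assumed correlation, equal SDs, normality and a two-sided 5% test against no difference; the textual conflict does not depend on them.

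**What to change.** Name one between-arm contrast and use it in Outcomes {12}, in the hypotheses under Sample size {14} and in Table 1 row 1a (title, hypothesis and measure).

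- **Preferred:** compare DDD at 6 months between arms in a linear model with baseline DDD as covariate. The treatment estimate and p value are then the same whether the outcome is coded as level or change, because subtracting baseline only shifts the baseline coefficient by one. Baseline DDD is already collected, and baseline adjustment is already planned as a sensitivity analysis, so this moves an existing analysis into the primary position.
- **Alternative:** keep change from baseline in DDD as defined in Outcomes {12}, and rewrite the hypotheses and row 1a as the between-arm difference in change. The downside should be stated: under the assumptions above, power falls below 80% once the correlation is under about 0.45.

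In either case, state which quantity the SD of 6.29 describes and restate the power for the chosen contrast. In the Discussion, replace the phrase about the pattern of alcohol use with the same DDD contrast.

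**Cost:** text edits, a revised power statement and, under the protocol's own rule, a formal amendment to the ethics committee, best made before outcome data are seen. No extra data are needed. The preferred option needs no more participants on this account; the raw change score might, if the correlation is low.

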## Trial status

Protocol version 1. April 10, 2020. Recruitment planned to start in September 2020 and last until September 2022.

## Abbreviations

ASI: Addiction Severity Index
AUD: Alcohol use disorder
AUDIT: Alcohol use disorders identification test
BMT: Brief motivational therapy
DALYs: Disability-adjusted life years
DDD: Drinks per drinking day
EUC: Enhanced usual care
FONDECYT: Fondo Nacional de Desarrollo Científico y Tecnológico
SDSS: Substance Dependence Severity Scale
DrInC: Drinker Inventory of Consequences
DSM-V: Diagnostic and Statistical Manual of Mental Disorders
MATCH: Matching Alcoholism Treatment to Client Heterogeneity
MD: Mean difference
MET: Motivational enhancement therapy
PC: Primary care
RA: Research assistant
RR: Relative risk
RRR: Relative risk reduction
SBIRT: Screening, brief intervention, and referral to treatment
SD: Standard deviation
SENDA: National service on drugs and alcohol (from the Spanish Servicio Nacional de Drogas y Alcohol)
TLFB: Timeline Follow Back
UKATT: United Kingdom Alcohol Treatment Trial
WAI—C/T: Working Alliance Inventory—client/therapist
